### Sample size and power calculation

The power calculation refers to the primary endpoint of the study, that is, change in total olfactory score (significant change defined as an increase of >12.5% on the maximum olfactory score, ie, >4 points on a theoretical maximum olfactory score of 32), during the single-blinded phase of the study (ie, the first 12 weeks of the study). The sample size was calculated based on a previous randomised controlled trial reporting clinically significant improvements on olfactory function in 28% of the OT group compared with 6% of the no-OT group after a 12‐week period.^38^ Assuming a drop-out ratio of 15%, we calculated a needed sample size of 100 participants.

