## Methods/design

### Subjects

In this ongoing trial, individuals with persisting COVID-19-associated OD will be included. All participants must be at least 18 years old. Pregnant women or individuals with a history of chronic OD will not be eligible. Female individuals who become pregnant during the study will be allowed to continue, but the data are planned to be excluded from final data analysis as pregnancy could impact olfaction. Persisting OD is defined as hyposmia or anosmia with a duration of at least 12 weeks after confirmed SARS-CoV-2 infection and established as a score of 12 or lower on the identification subscale of the Sniffin’ Sticks testing battery. Prior SARS-CoV-2 infection will preferably be verified by a positive PCR result but can also be established by positive serum levels of antibodies towards SARS-CoV-2 nucleocapsid antigens. All participants are scheduled to undergo routine ENT examination, including anterior rhinoscopy, to exclude non-COVID-19-related pathologies causing OD. There will be no prohibited medication during the trial. A full list of inclusion and exclusion criteria can be found in table 1.

**Table 1 T1:** Overview of inclusion and exclusion criteria

Inclusion criteria	Exclusion criteria
Subject is 18 years or older Confirmed COVID-19 infection by either: PCR results from date of infection Serum antibodies against SARS-CoV-2 nucleocapsid antigens Postinfectious COVID-19-associated OD <13/16 items correct on identification part of the Sniffin’ Sticks Participant is willing to undergo olfactory training over 12 weeks Written ICF is obtained	History of OD prior to COVID-19 infection Nasal pathologies not related to COVID-19 Pregnancy

ICF, informed consent form; OD, olfactory dysfunction.

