### Trial design and safety measurements

The SMELL study is a monocentric trial assessing OT in individuals with persisting COVID-19-associated OD. This study is designed to encompass a screening/baseline visit, followed by a final visit after 12 weeks (day 84+14 days). Written informed consent will be obtained at baseline by a member of the study team (see online supplemental material, available in German). Demographic data and comorbidities are planned to be gathered at the baseline visit through a structured interview. Multiple questionnaires and scales will be completed at this visit. Randomisation is planned after establishing the diagnosis of OD, with one group starting OT immediately after the baseline visit.

OT is set to be performed by the patients after thorough instruction using the Sniffin’ Sticks Duft Quartett, a training kit containing four pens with a distinct scent (clover, eucalyptus, rose and lemon), for 15 min two times per day over a period of 12 weeks. No check-ups between visits will be organised. The same questionnaires and assessments are intended to be conducted at the final visit (day 84+14 days). While this will mark the end of the study for the training cohort, the second cohort will be offered to participate in an open extension phase, performing OT. They will have a third/follow-up visit after another 12 weeks (day 168+14 days). Treatment adherence is planned to be checked using a diary, which will be handed out at baseline, where participants have to check the boxes each day to confirm training. A good compliance is defined as training performance >80% over 12 weeks.

Each adverse event (AE) is expected to be noted in the case report form (CRF), while severe AEs will be reported to the sponsor of the study. Should a subject request or decide to withdraw from the study, all efforts are expected to be made to complete and report the observations as thoroughly as possible up to the end of withdrawal. A safety follow-up will be scheduled for participants who received OT. The primary reason is intended to be stated in the CRF. The sponsor will be authorised to discontinue the study due to relevant medical or administrative causes (eg, insufficient recruitment of participants, non-resolvable problems of data quality and occurrence of unacceptable risks and toxicities). A comprehensive overview of the study flow, completed tests and questionnaires can be found in figure 1 and table 2.

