### Statistical rationale and outcomes

The primary endpoint of this study refers to the change in total olfactory score between baseline visit and final visit (84 days+14). Statistical analysis is planned to be performed after study completion. No interim analysis of OT efficacy will be performed. Secondary endpoints will be the changes on the multiple questionnaires and scales between baseline and final visit, with gender-related differences as an exploratory endpoint. The questionnaires will include the SF-36 questionnaire (36-item Short Form Survey) and the Hospital Anxiety and Depression Scale (HADS), which is a reliable instrument for detecting states of anxiety and depression in the setting of the hospital outpatient clinic.^30^,^32^ We will also include a German questionnaire focussing on personal well-being (‘Befindlichkeitsskala’), which was shown to be sensitive for change over a short time, and a 10-point visual analogue scale of olfactory function.^33^ Symptom severity will be assessed using Clinical and Personal Global Impression of Severity at each visit. The patient global impression of improvement/clinical global impression of improvement (PGI-I/CGI-I) is intended to be only performed at the final visit after 12 weeks and the follow-up visit after another 12 weeks, if applicable. A descriptive analysis (χ^2^ test for categorical variables, Mann-Whitney U test or unpaired t-test for continuous variables depending on the scale type of the variables) of demographic and clinical data at baseline will be performed. Secondary efficacy criteria will be measured as the change in the other clinical scales and questionnaires between baseline and week 12, except for the PGI-I and CGI-I measures, which will be singularly evaluated at week 12. These measurements are particularly useful as they have been used in clinical studies recruiting patients with different disorders.^34^,^37^ For the analysis of the primary endpoint, we intend to fit a repeated-measures mixed model olfactory function (Sniffin’ Sticks test score) as the dependent variable and a factorial interaction, with between group assignment (training, control) and time (before and after OT) as independent variables. Changes in the total olfactory score (combination of the identification and discrimination subscale of the Sniffin’ Sticks testing battery) and the different scales and questionnaires used in this trial will be given as mean with 95% CI. The same model is planned to be used for the analysis of change of secondary outcome measures (Mood Inventory (Befindlichkeitsskala, Bf-S), Hospital Anxiety and Depression Scale (HADS), Short-Form-36 Health Survey Questionnaire (SF-36)). Comparison will be performed with the χ^2^ test. The PGI-I and CGI-I, which will be singularly evaluated at week 12, will be compared by the non-parametric Mann–Whitney U test. For PGI-I and CGI-I analyses, distributions of dichotomised ratings (amelioration, aggravation) in both groups at the 12-week termination visit will also be compared by the χ^2^ test. For all analyses, statistical significance will be set at the two-sided 5% level.

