
Missing, unused or spurious primary efficacy data will lead to exclusion of the respective study participant for statistical analysis (eg, drop-out or non-compliance to treatment). Other missing, unused or spurious data will lead to the exclusion of the respective variable for further statistical analysis. Due to the design of the study with assessment of all efficacy variables at only two time points, the primary analysis is intended to be a per-protocol analysis. Therefore, an interpolation of data will not be performed in case of drop-out.

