### Study setup/workflow

Permission for trial performance was given by the ethics committee of the MUI (reference number: 1273/2020). An amendment to include positive serology for antibodies towards nucleocapsid-antigens to establish previous COVID-19 infection was later approved by the ethics committee of the MUI (table 3). Patient recruitment was initiated in August 2022 and is completed. Results of the study are expected later in 2025. The study is registered on ClinicalTrials.gov (NCT05421221).

**Table 3 T3:** Summary of the trial, conform the WHO trial registration data set (V.1.3.1)

Data category	Information
Primary registry and trial identifying number	Federal Office for Safety in Health Care Austria (Bundesamt für Sicherheit im Gesundheitswesen, BASG), 12 732 020
Date of registration in primary registry	16 May 2022
Secondary identifying numbers and registry	ClinicalTrials.gov: NCT05421221 (registration: 13 June 2022)
Source of monetary or material support	Austrian Science Fund (FWF)
Primary sponsor	Medical University of InnsbruckAnichstraße 356020 InnsbruckAustriaE-Mail: [contact]
Secondary sponsor	None
Contact for public and scientific queries(PI and author of the study protocol)	[name] ([contact])Medical University of InnsbruckBH, MD PhD ([contact])Medical University of Innsbruck
Public title	Olfactory Training in COVID-19-Associated Loss of Smell
Scientific title	A randomised controlled trial of the effectiveness of olfactory training on loss of smell related to COVID-19 (SMELL)
Country of recruitment	Austria
Health condition studied	Persisting COVID-19-associated loss of smell
Interventions	Active comparator: olfactory training using the Sniffin’ Sticks Duft Quartett. Duration of 12 weeks (2×/ day)Passive comparator: no changes in daily routine.
Key inclusion and exclusion criteria	Inclusion criteria: prior history of COVID-19 infection (>3 months before study participation) and olfactory dysfunction (score<13/16 on the identification subscale of the Sniffin’ Sticks)Exclusion criteria: history of olfactory dysfunction, nasal pathologies not related to COVID-19, pregnancyA full overview can be found in table 1
Study type	InterventionalAllocation: randomisedSingle-blinded study (investigator)Intervention model: parallel assignmentPrimary purpose: treatmentPhase II
Date of first enrolment	August 2022
Target sample size	Total of 100 participants (1:1 randomisation)
Recruitment status	Completed

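### The 15% allowance in the sample size is for drop-out only and is not shown to cover the non-compliance and pregnancy exclusions of the primary per-protocol analysis

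*Protocol article*

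**What the plan says.** **Sample size.** The section *Sample size and power calculation* of the Protocol article takes its effect from an earlier randomised trial that reported "clinically significant improvements on olfactory function in 28% of the OT group compared with 6% of the no-OT group after a 12‐week period". It then makes a single adjustment for loss: "Assuming a drop-out ratio of 15%, we calculated a needed sample size of 100 participants". The registration summary (Table 3) repeats the target: "Total of 100 participants (1:1 randomisation"). No power is stated.

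**Analysis set.** The last paragraph of *Statistical rationale and outcomes* makes the per-protocol analysis primary. Missing, unused or spurious primary efficacy data lead to exclusion of the participant "for statistical analysis (eg, drop-out or non-compliance to treatment"). Drop-out and non-compliance are thus named side by side.

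**Compliance.** *Trial design and safety measurements* gives the only threshold, to be read from a diary: "A good compliance is defined as training performance >80% over 12 weeks". It adds that there will be no check-ups between visits.

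**Pregnancy.** Under *Subjects*, women who become pregnant during the study may continue, but "the data are planned to be excluded from final data analysis as pregnancy could impact olfaction".

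The article gives no expected rate for non-compliance, pregnancy or unusable data.

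**The concern.** The calculation budgets for one kind of loss, and the primary analysis set applies several. Whether 100 enrolled participants leave enough to analyse depends on losses for which the plan makes no stated allowance.

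The main one, non-compliance, is also one-sided. Controls have no training to comply with in the first 12 weeks, so every compliance exclusion comes out of the training arm. The article itself gives reason to expect some: training is 15 minutes twice daily for 12 weeks without interim contact, and the Background cites an earlier training trial whose authors put its null result down to low compliance.

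At stake is how a null per-protocol result would be read. It could be presented as coming from a trial sized for its question, when the analysed number had fallen below the one behind the calculation.

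**Working it through.** **Inputs**
- Response rates 28% and 6%, difference 0.22 (*Sample size and power calculation*).
- Two-sided 5% (*Statistical rationale and outcomes*: "For all analyses, statistical significance will be set at the two-sided 5% level").
- Drop-out 15%, total 100, allocation 1:1.
- Power: not stated. 80% is assumed because it reproduces the 100.
- Non-compliance rate: not stated. A range is shown.

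**1. Reproduce the 100**

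Two proportions, unpooled variance:

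n per arm = (1.96 + 0.8416)² × (0.28 × 0.72 + 0.06 × 0.94) / 0.22²
= 7.849 × (0.2016 + 0.0564) / 0.0484
= 41.84, so 42 per arm, 84 in all.

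84 / 0.85 = 98.8. Per arm, 42 / 0.85 = 49.4, so 50, giving **100**. The figure reproduces.

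Other two-sided variants at 80% power give totals of 98 (arcsine), 106 (pooled) and 128 (continuity-corrected). At 85% or 90% power, every two-sided variant gives 112 or more. The match therefore rests on 80% power and the unpooled formula.

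**2. Slack**

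100 × 0.85 = 85 analysable, against 84 needed. The largest total loss that still leaves 84 is 1 − 84/100 = 16%. If drop-out takes its planned 15%, one further exclusion is absorbed and a second is not.

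**3. Adding non-compliance**

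Take 42 per arm after drop-out, then remove an assumed share of the trainees only. Unpooled power is

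Φ( 0.22 / √(0.2016/n₁ + 0.0564/42) − 1.96 ).

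For n₁ = 34: √(0.005929 + 0.001343) = 0.0853; 0.22 / 0.0853 = 2.58; Φ(0.62) = 73%.

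The exact column is the power of the Pearson chi-square test, summed over all binomial outcomes.

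| Assumed non-compliance in training arm | Training / control analysed | Unpooled power | Exact power |
|---|---|---|---|
| 0% | 42 / 42 | 80% | 81% |
| 10% | 38 / 42 | 77% | 79% |
| 20% | 34 / 42 | 73% | 77% |
| 30% | 30 / 42 | 69% | 73% |
| 40% | 26 / 42 | 64% | 70% |

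Adding an assumed 1-2% of pregnancy exclusions costs less than one further point.

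**4. What happens if non-compliers are kept**

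Suppose 28% is the rate among compliers and non-compliers respond like controls, at 6%. With 20% non-compliance the training-arm rate is 0.80 × 28% + 0.20 × 6% = 23.6%. Power at 42 / 42 is then 65% (unpooled) or 67% (exact). If 28% already includes non-compliers, this dilution does not apply.

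**The case against.** **The 15% may be shorthand for all losses.** The missing-data paragraph gives drop-out and non-compliance as examples of one class of exclusion, and the article condenses a fuller protocol. This is possible, but the article does not say so, and elsewhere it uses the two words separately. The allowance is therefore not shown to be sufficient; it is not proven insufficient.

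**A reader might infer that 100 participants cannot deliver the number needed.** The documents do not support that. A shortfall needs total loss above about 16%, and no non-compliance or pregnancy rate is given. The earlier trial with low compliance recruited people with major depressive disorder, and the article reports no rate from it. If all exclusions together stayed within 15%, 100 would suffice.

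**A reader might also infer that the planned primary test is underpowered.** That does not follow either. The calculation concerns responder proportions, whereas the primary analysis is a mixed model on the score. If changes were normal with equal SD, 28% against 6% would correspond to a standardised difference of about 0.97. A two-sample t-test on change would then have 99% power at 42 / 42 and 97% even at 26 / 42. This rests on assumptions that the article does not make, but it shows that the table above cannot be carried over to the mixed model.

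**The likely effect is small.** At 10% non-compliance the loss is about 2 to 3 points. This stands as a limit on severity. It does not remove the mismatch between the allowance and the analysis set.

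**Conclusion.** The point holds in limited form. The arithmetic behind 100 is sound for 15% drop-out, with a slack of one participant. The primary per-protocol set removes participants for further reasons, and no stated allowance covers them. With 15% drop-out and 10-20% non-compliance among trainees, the responder calculation would have about 77-73% power (unpooled) or 79-77% (exact), against an implied 80-81%. Pregnancy is a minor contributor.

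This rests on an inferred 80% power, on assumed non-compliance rates, and on drop-out using its full 15% in both arms. It should be corrected before the results are read, but it does not invalidate the trial. The one-sidedness of the compliance exclusion is a reason to change the primary set whatever its effect on power.

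**What to change.** Recruitment is reported as complete, so do not enrol more. There are two ways to reconcile the text.

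**Preferred.** Make the primary analysis all randomised participants with a week-12 score, analysed as randomised and regardless of diary compliance or pregnancy, with the per-protocol analysis as supportive. Missing week-12 data are then the only loss, which is what a drop-out allowance describes, and the exclusion that falls only on the training arm disappears. Do not state that the original power is preserved: non-compliers may dilute the effect (step 4 of the working).

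**If per-protocol stays primary.** Restate the sample-size paragraph. Name the combined loss assumed (drop-out, compliance of 80% or less, pregnancy, unusable data) and give the power that 100 participants then provide.

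Either change costs one or two sentences and no new patients. The second also means stating a less favourable power if the combined loss assumed exceeds about 16%.

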### Study setup/workflow

Permission for trial performance was given by the ethics committee of the MUI (reference number: 1273/2020). An amendment to include positive serology for antibodies towards nucleocapsid-antigens to establish previous COVID-19 infection was later approved by the ethics committee of the MUI (table 3). Patient recruitment was initiated in August 2022 and is completed. Results of the study are expected later in 2025. The study is registered on ClinicalTrials.gov (NCT05421221).

**Table 3 T3:** Summary of the trial, conform the WHO trial registration data set (V.1.3.1)

Data category	Information
Primary registry and trial identifying number	Federal Office for Safety in Health Care Austria (Bundesamt für Sicherheit im Gesundheitswesen, BASG), 12 732 020
Date of registration in primary registry	16 May 2022
Secondary identifying numbers and registry	ClinicalTrials.gov: NCT05421221 (registration: 13 June 2022)
Source of monetary or material support	Austrian Science Fund (FWF)
Primary sponsor	Medical University of InnsbruckAnichstraße 356020 InnsbruckAustriaE-Mail: [contact]
Secondary sponsor	None
Contact for public and scientific queries(PI and author of the study protocol)	[name] ([contact])Medical University of InnsbruckBH, MD PhD ([contact])Medical University of Innsbruck
Public title	Olfactory Training in COVID-19-Associated Loss of Smell
Scientific title	A randomised controlled trial of the effectiveness of olfactory training on loss of smell related to COVID-19 (SMELL)
Country of recruitment	Austria
Health condition studied	Persisting COVID-19-associated loss of smell
Interventions	Active comparator: olfactory training using the Sniffin’ Sticks Duft Quartett. Duration of 12 weeks (2×/ day)Passive comparator: no changes in daily routine.
Key inclusion and exclusion criteria	Inclusion criteria: prior history of COVID-19 infection (>3 months before study participation) and olfactory dysfunction (score<13/16 on the identification subscale of the Sniffin’ Sticks)Exclusion criteria: history of olfactory dysfunction, nasal pathologies not related to COVID-19, pregnancyA full overview can be found in table 1
Study type	InterventionalAllocation: randomisedSingle-blinded study (investigator)Intervention model: parallel assignmentPrimary purpose: treatmentPhase II
Date of first enrolment	August 2022
Target sample size	Total of 100 participants (1:1 randomisation)
Recruitment status	Completed
Primary outcome	Difference in change of total olfactory score between baseline visit and final visit (84+14 days) between both cohorts
Secondary outcome	Change in subjective olfactory score (VAS) between baseline visit and final visit (84+14 days)Patient/clinical global impression of improvement (PGI-I and CGI-I) at final visit (day 84+14 days)Changes in mood and personal well-being (HADS-A, HADS-D and BF-SR) between baseline visit and final visit (84+14 days)Changes in daily function (SF-36) between baseline visit and final visit (84+14 days)
Exploratory outcome	Gender-related differences on OD and OT
Ethics revision chronology	Name: Ethics Commission of the Medical University of InnsbruckContact: [contact] October 2020: approval of original protocol15 November 2021: Amendment 1: addition of routine otolaryngological examination to exclude non-COVID-19-related nasopharyngeal pathologies19 April 2022: Amendment 2: elongation of study duration till 202518 April 2023: Amendment 3: serum antibodies towards nucleocapsid were added for future participants without PCR results (V.2.3–16 March 2023, current version)12 December 2023: Amendment 4: amendment to publish a call for new participants
IPD sharing statement	Data supporting the results will be archived in an appropriate public repository

BF-SR, Befindlichkeitsskala; FWF, Österreichischer Wissenschaftsfonds; HADS-A, anxiety subscale of the HADS-questionnaire; HADS-D, depression subscale of the HADS-questionnaire; OD, olfactory dysfunction; OT, olfactory training; SF-36, 36-item Short Form Survey; VAS, visual analogue scale.

### Ethics and dissemination

Ethical approval was obtained from the Ethics Commission of the Medical University of Innsbruck (MUI), Austria, in 2022. All changes to the study must be approved by the Ethics Commission by submitting an amendment. An amendment regarding patient recruitment was approved by the ethical board, allowing the study team to publish a call for participants in the local newspaper, stating the aim and short description of the study. The results of this study will be published by members of the study team in accordance with the principles of publication policy and through scientific conferences. There is no intended use of professional writers. Study participants will not specifically be informed about the study results.

